### Randomisation and blinding

The randomisation schedule will be prepared using numbered and sealed, opaque envelopes. Participants will be randomly allocated in a 1:1 ratio to either the ‘Maxm Skate Rehabilitation Program’ or the ‘Standard Rehabilitative Care’ group. Block randomisation in groups of four will be used to ensure balance in the two groups. Randomisation will also be stratified by gender to ensure balance between groups for each gender. We note that the number of women undergoing TKA for osteoarthritis has been shown to be greater in Australia [21]. In addition, studies have demonstrated that there are differences between men and women in muscle and physical function recovery after TKA [22, 23].

The study will be single-blinded with blinding of study investigators but not participants. Participant randomisation to either Maxm Skate or Standard Care will be performed by the unblinded Study Coordinator, who will hold the treatment allocation code in confidence. The statistician will be blinded to the treatment allocation code when performing all analyses. Functional evaluations and performance tests will be conducted by a trained physiotherapist ([name]) who will be blinded to group allocation. This blinded physiotherapist will conduct all functional evaluations, excluding postoperative day 2, due to practical constraints. Non-blinded ward-based physiotherapists will conduct the day 2 assessments, as well as the preoperative Maxm Skate education session for participants allocated to the Maxm Skate group.

Due to the nature of the intervention there is a potential for participants to disclose, or physiotherapist to gauge, which group the participants are assigned. Participants will be educated and instructed not to advise the physiotherapist or treating surgeon of their group assignment at the time of their consent and randomisation with the unblinded Study Coordinator. However, if participants are concerned about their rehabilitative progress and feel it is necessary to discuss this with their treating surgeon, they will be able to do so. The breaking of blinding will be collected and reviewed during data analysis.

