### Recruitment and selection criteria

Consecutive patients consented for elective primary TKA at a single orthopaedic surgeon’s private clinic will be screened for eligibility. The treating surgeon ([name]) will screen all patients against the selection criteria and document reasons for ineligibility in the patient screening log. Study inclusion criteria include:The patient requires a primary TKA due to non-inflammatory degenerative joint disease (e.g. osteoarthritis and traumatic arthritis) or inflammatory joint disease (e.g. rheumatoid arthritis).The patient must understand the conditions of the study and be willing and able to provide written informed consent.The patient is a skeletally mature man or a non-pregnant woman, aged ≥ 30 years.The patient agrees to comply with the specified preoperative and postoperative study requirements.

Study exclusion criteria include:The patient has an emotional or neurological condition that would pre-empt their ability to participate in the study including mental illness, intellectual disability and drug or alcohol abuse.Any patient who is unable to meet the requirements of the use of the Maxm Skate Rehabilitation Device.The patient is unable to perform home exercise program without supervision or assistance.

A clinical nurse or authorised delegate will invite eligible patients to come in to discuss the study. Patients will be informed of the study purpose and the potential risks and benefits known, or that can be reasonably predicted, as outlined in the Participant Information Sheet.

The patient will then be given the opportunity to ask any clarifying questions and invited to complete the consent form, indicating their understanding of the study and consent for participation. Following consent, participants will be randomised and baseline measures obtained. The randomisation number will be used to provide anonymous identification of the participant on study documents from there forth.

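### A single published block size of four lets the unblinded coordinator, who is with participants at consent, know about a third of allocations in advance

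*Protocol article*

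**What the plan says.** Everything on sequence and concealment is in the protocol article, section Randomisation and blinding.

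- Ratio and blocks: "Participants will be randomly allocated in a 1:1 ratio", and "Block randomisation in groups of four will be used to ensure balance in the two groups". No other block size is mentioned.
- Stratification: "Randomisation will also be stratified by gender to ensure balance between groups for each gender".
- Concealment: "The randomisation schedule will be prepared using numbered and sealed, opaque envelopes".
- Who randomises: this "will be performed by the unblinded Study Coordinator, who will hold the treatment allocation code in confidence".
- Who is present: participants are told not to reveal their group "at the time of their consent and randomisation with the unblinded Study Coordinator".
- Blinding: "The study will be single-blinded with blinding of study investigators but not participants".

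The section Recruitment and selection criteria adds that patients are consecutive and come from one surgeon's clinic. The surgeon "will screen all patients against the selection criteria and document reasons for ineligibility in the patient screening log", a clinical nurse or delegate invites those who are eligible, and randomisation follows consent. The Statistical methods section makes the primary comparison an unadjusted two-sample test; baseline characteristics, including ROM, enter in a sensitivity analysis.

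**The concern.** Concealment has two parts: nobody can see the next assignment, and nobody can work it out. Opaque envelopes secure the first part only. In a 1:1 block of known size, the allocations already made determine some of those still to come.

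Here the conditions for working it out meet in one person. The coordinator performs randomisation, so knows every earlier allocation, and also knows each participant's gender and therefore the stratum. With one site there is a single running sequence per gender, and the block size is in print. The same person is with the participant at consent.

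At stake is the comparability of the groups. If the next arm is known, the way participation is presented, or when the appointment takes place, can shift without anyone intending it. Entry here includes willingness to comply and ability to use the device, so the conversation is not a pure formality. Because the primary test is unadjusted, any imbalance produced in this way would pass straight into the primary result.

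**Working it through.** **Inputs.** Block size 4, ratio 1:1, two gender strata (Randomisation and blinding); 116 participants (Sample size). The article gives no figure for predictability. Its sample size reproduces: with a difference of 10°, SD 16°, two-sided 5% and 90% power, the t-based solution is 54.78, so 55 per group and 110 in total; 110 / 0.95 = 115.8, so 116. The present point does not affect it.

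**Step 1: certain allocations within one block.** There are six equally likely orders of two A and two B. For someone who knows the earlier allocations in the block:

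| Position | Next allocation is certain when | Probability |
|---|---|---|
| 1 | never | 0 |
| 2 | never | 0 |
| 3 | the first two are the same (AA or BB: 2 of 6 orders) | 1/3 |
| 4 | always | 1 |

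Share certain = (0 + 0 + 1/3 + 1) / 4 = 1/3 = 33.3%.

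**Step 2: scale to 116.** If every block is complete there are 116 / 4 = 29 blocks and 29 × 4/3 = 38.7 certain allocations. If each stratum ends two participants into a block, there are 28 complete blocks and 28 × 4/3 = 37.3, or 32.2%. If one stratum ends one in and the other three in, the figure is 37.3 + 1/3 = 37.7. The range is therefore 37.3 to 38.7. Simulation of 3,000 trials gave 32.7% (37.9 of 116) with equal genders on average and 32.6% (37.8) with a 60:40 split.

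**Step 3: does varying the block help?** Block sizes were drawn with equal probability, separately in each stratum. The observer was assumed to know the possible sizes but not their order. An allocation counted as certain only if every block structure consistent with the history gave the same arm.

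| Block sizes | Certain in advance | Of 116 |
|---|---|---|
| 4 fixed | 32.7% | 37.9 |
| 4, 6 | 5.5% | 6.4 |
| 2, 4, 6 | 4.0% | 4.7 |
| 4, 6, 8 | 2.4% | 2.8 |

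A larger fixed block helps much less: 25% certain for blocks of 6 and 20% for blocks of 8. An observer who does not know the possible sizes cannot be certain more often than one who does, so the figures for varying blocks are upper limits once the sizes are withheld.

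**Step 4: best-guess accuracy.** Guess the arm that is behind, and toss a coin when the arms are level. For blocks of 4 this is (1/2 + 2/3 + 2/3 + 1) / 4 = 70.8%. For blocks of 2, 6 and 8 it is 75.0%, 68.3% and 66.6%. Weighted by block length:

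- 2, 4, 6: (2 × 0.750 + 4 × 0.708 + 6 × 0.683) / 12 = 70.3%
- 4, 6, 8: (4 × 0.708 + 6 × 0.683 + 8 × 0.666) / 18 = 68.1%

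This strategy needs only the running count, because every block ends level. Withholding the sizes does not defeat it.

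**The case against.** Fixed blocks of four with numbered, sealed, opaque envelopes are a recognised design, and the article describes real safeguards. Patients are consecutive. The surgeon decides eligibility, logs exclusions and is meant to be blinded. A nurse or delegate makes the invitation. Consent comes before randomisation. Nothing gives the coordinator a part in deciding who is eligible. All of this stands, and it reduces the exposure to the consent conversation and its timing. It does not remove it, because the person with foreknowledge is there.

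A reader might infer more than the article supports, in five ways.

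- *That the surgeon or the assessing physiotherapist can also predict allocations.* Both are meant to be blinded, and the one-third figure requires knowledge of every earlier allocation in the stratum. Nor does the lack of participant blinding matter much here: a participant knows one assignment, not the sequence.
- *That the trial will be biased.* The 37 to 39 are predictable allocations, not biased ones. No effect on ROM has been estimated.
- *That no analysis could repair the damage.* The planned baseline-adjusted sensitivity analysis can reduce imbalance in measured characteristics, including baseline ROM. It cannot reach unmeasured ones.
- *That 71% correct guessing against 50% makes the case for varying blocks.* The 50% belongs to simple randomisation. Step 4 shows that varying blocks leave the figure at about 68–70%.
- *That the coordinator holds the whole list, so that far more than a third is known.* The wording about holding the code does not establish this. Who generates the list, and how, is a detail that a condensed article may leave to the full protocol, so its absence is no defect.

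**Conclusion.** The point holds for the coordinator. With one published block size of four within gender, about one third of allocations (33.3% in complete blocks; 37 to 39 of 116) are certain to that person before assignment, whatever the envelopes look like. This is a stated design choice that weakens concealment; it is neither a contradiction nor evidence of selection. It merits a change because the remedy is cheap and the present exposure serves no purpose: balance does not require a block of constant, known size.

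The conclusion rests on three assumptions. The coordinator knows all earlier allocations by gender, which follows from performing randomisation and holding the code. Four is the only block size used, as the article states. The coordinator takes part in consent as well as randomisation, which is the natural reading of the sentence on participant instruction. If the coordinator were in fact absent until consent had been signed, the opportunity would shrink to the timing of randomisation.

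**What to change.** Keep 1:1 allocation and stratification by gender. Replace the fixed block with block sizes that vary at random within each stratum, for example 4, 6 and 8, or 2, 4 and 6, for all participants or, if recruitment has begun, for all who remain. Withhold the sizes from the coordinator, state only that they vary, and publish them after recruitment ends. Certain allocations fall from about 32–33% to about 2–4% (3 to 5 of 116), even if the possible sizes become known.

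The cost is a new list and a short amendment. Final imbalance may be slightly larger: an unfinished block can leave a stratum uneven by at most half its length, so the limit across two strata rises from 4 participants (2 + 2) with blocks of four to 6 (3 + 3) with blocks up to six, or 8 (4 + 4) with blocks up to eight. The sample size calculation needs no change.

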### Interventions

All participants will undergo primary TKA at Flinders Private Hospital. All hospital TKA patients are invited to attend a ‘Joint replacement information session’ which provides further education and the opportunity for physiotherapy and nursing staff to address patient queries. An exercise booklet is issued describing the postoperative exercises and patients are asked to familiarize themselves with the exercises.

#### Maxm Skate rehabilitation program

Participants randomised to the Maxm Skate rehabilitation program will be required to use the skate device and accompanying iOS App and sensors to complete rehabilitation exercises, as outlined in the *Maxm Skate Rehabilitation Guide* (see Additional file 1). Participants will be asked to download the Maxm Skate App on an iOS device, which will be provided if a personal device is not available.

Clinical data will be collected via the App aligns with the exercises outlined in the rehabilitation guide, including exercises completed, number of repetitions, length of time completing exercise and outcomes achieved. Data collected via the App are stored in the Google Firestore cloud database and within the iOS device itself.

##### Preoperative phase

Participants will attend a preoperative device education session where they will be introduced to the Maxm Skate program by a physiotherapist. Participants will be given a description of the functionality, set up and safe usage of the Maxm Skate device and sensor, and educated on the Maxm Skate exercise program. Following this presentation, participants will be issued with a rehabilitation guide to familiarise themselves with the postoperative exercise program and given the opportunity to trial the skate package.

##### Postoperative inpatient phase

In the inpatient acute setting, the Maxm Skate group will receive the Maxm Skate in addition to standard care as outlined above for the Standard Care group. The Maxm Skate group may access inpatient rehabilitation if clinically indicated.

##### Postoperative outpatient phase

Following the inpatient program, participants in the Maxm Skate program will only receive rehabilitation provided through the Maxm Skate program, described in the *Maxm Skate Rehabilitation Guide* (see Additional file 1). This program includes functional assessment checks at two weeks and six weeks at the participant’s home. This will ensure participants are fit to progress through from Stage One to Stage Two and from Stage Two to Stage Three of the program. Additional functional checks will be conducted if required, as assessed by hospital staff at discharge from hospital. Furthermore, the checks will allow early identification of participants who are not advancing and may require additional rehabilitative support.

Participants that are identified as requiring additional physiotherapy will receive such treatment, as required. Participant functional progress will also be assessed by the orthopaedic surgeon at the six-week orthopaedic follow-up appointment. Any additional outpatient physiotherapy received by a participant randomised to the Maxm Skate program will be permitted and recorded in the participant study file.

#### Standard rehabilitative care

Inpatient physiotherapy care provided to patients in hospital will include undertaking the following standard care exercises: ankle pumps; static quadriceps; supine knee flexion; inner range quadriceps; straight leg raise; passive knee extension; seated assisted knee flexion; and active knee extension in sitting. Once discharged from hospital, physiotherapy follow-up varies on an individual basis. The patient is provided four patient-specific options which are described in the *Outpatient Standard Care Physiotherapy Protocol* (*FPH*) (see Additional file 2).

### Study outcomes and participant timeline

The primary objective is ROM achieved at three months after TKA. Secondary outcomes include patient-reported outcomes, costs and functional evaluations which will be collected at multiple time-points up to 12 months after TKA. Patients will be screened for AE occurrences and complications from the time of consent to one year postoperatively. The study assessment schedule in outlined in Fig. 1.

**Fig. 1 Fig1:**
[figure not shown]
Schedule of events

#### Baseline and operative data

Demographic details, knee pathology and medical history will be collected preoperatively by the clinical nurse or research delegate.

In order to limit any potential variability attributed to the prosthetic device, a single total knee prosthesis, the Advanced Coated System ACS® Fixed Bearing System (Oceania Orthopaedics Pty. Ltd.) will be implanted in all study participants by a single orthopaedic surgeon ([name]). The medical device will be implanted using a medial para-patella surgical approach, using both a cemented and cementless technique depending on patient characteristics and surgeon discretion. A midline skin incision will be conducted for all patients and device-specific instrumentation will be used.

#### Patient-reported outcome measures

Patient-reported outcome measures will be assessed for each group preoperatively and postoperatively at six weeks, 12 weeks and 12 months. The Oxford Knee Score (OKS) [24] and Knee Injury and Osteoarthritis Outcome Score (KOOS) [25] will be used to assess knee-specific symptoms, pain and function, while the Euroqol 5 Dimensional Health Survey – Level 5 (EQ-5D-5L) [26] will be used to survey health status. The Patient Acceptable Symptom State (PASS) [27] will be used to assess whether the patient feels that they are at a satisfactory state. Lastly, level of satisfaction with the outpatient rehabilitation received will be measured using a 5-point Likert scale as follows: ‘very unsatisfied’; ‘unsatisfied’; ‘neither satisfied nor unsatisfied’; ‘satisfied’; ‘very satisfied’.

Participants in the Maxm Skate group will also be required to complete a short questionnaire regarding their participation in the Maxm rehabilitation program. This form will be administered at a visit with the Study Coordinator either before or after each functional evaluation with the blinded physiotherapist.

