**Methods:**

This is a single-blinded, randomised controlled trial (RCT) in which 116 eligible participants consented for primary TKA will be randomly allocated to receive either the Maxm Skate rehabilitation program or standard rehabilitative care. Fifty-eight participants per group will provide 90% power (α = 0.05) to detect 10° of difference in ROM between groups at three months after TKA, assuming a within-group standard deviation of 16° and allowing for 5% loss to follow-up. Participants randomised to the Maxm Skate group will use the skate device and accompanying iOS App and sensors to complete rehabilitation exercises, as outlined in the *Maxm Skate Rehabilitation Guide*. Outcomes will be compared to those receiving standard rehabilitative care.

A blinded physiotherapist will evaluate functional outcomes preoperatively and at 2, 4, 6, 12, 26 and 52 weeks after TKA. The functional assessment will include measures of knee ROM, pain, isometric knee strength, balance and knee/thigh circumference. Limited measures will also be assessed at day 2 postoperatively by an alternate, unblinded physiotherapist. Clinical outcome measures will be administered preoperatively and at 6, 12 and 52 weeks postoperatively. An economic evaluation will be conducted and participants will be screened for adverse event occurrences from the time of consent to 12 months postoperatively.

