#### Functional evaluations

The following functional evaluations will be performed by a blinded physiotherapist preoperatively and at 2, 4, 6, 12, 26 and 52 weeks after TKA. Some measures will also be assessed at day 2 postoperatively; however, these measures will be taken by an unblinded ward physiotherapist. Functional evaulations are illustrated in Fig. 2.

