#### Economic evaluation

An economic evaluation assessing the relative cost-effectiveness of the Maxm Skate rehabilitation device compared to standard care will be conducted.

This analysis will take the form of an economic evaluation comparing the relative cost-effectiveness analysis of the Maxm Skate rehabilitation device to standard care using data collected during the trial. The primary outcome will be the incremental cost per unit increase in knee ROM while a secondary outcome will be the incremental cost per quality-adjusted life year (QALY) gained over the period of the primary study and based on the EQ-5D-5 L. As an Australian scoring algorithm for the EQ-5D-5 L is not yet available, the UK value set and scoring algorithm [36] will be used to convert the individual responses to the EQ-5D-5 L at each time point. Resource use associated with each trial arm will be combined with unit costs for these resources in order to estimate total costs in the trial. Costs will be estimated from a societal perspective (to include costs borne by private hospitals and insurance providers, private patients and social care service providers). Resource use data will include a number of tests, treatments and investigations undertaken during in-hospital visits, the frequency and duration of in-hospital admissions, over the counter medication, lost productivity, social care services, as well as quantity and type of consumables and equipment used. Resource use data to capture patient-specific costs incurred will only be collected after discharge, using a resource use questionnaire that will be administered at 2, 4, 6, 12, 26 and 52 weeks. Resource unit costs will be derived from hospital finance departments and supplemented, where necessary, by information from published source including the Australian Bureau of Statistics and Australian Refined Diagnosis Related Groups (AR-DRG) cost weights. Confidence intervals will be presented around the incremental cost-effectiveness ratios and cost-effectiveness acceptability curves for varying threshold values of cost-effectiveness will also be presented [37]. An assessment of the sensitivity of the results obtained to variation in measured resource use, effectiveness and/or unit costs will be undertaken using appropriate deterministic and probabilistic sensitivity analyses [38].

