### Study duration

The study accrual period will be approximately 12 months. Each individual will be followed for 12 months.

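### The EQ-5D-5L is not collected at 26 weeks, although participants attend and report resource use then, so no utility is observed for 40 of the 52 weeks behind the cost-per-QALY outcome

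*Protocol article*

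**What the plan says.** The section on patient-reported outcome measures covers the OKS, KOOS, EQ-5D-5L, PASS and satisfaction with rehabilitation under one schedule: "Patient-reported outcome measures will be assessed for each group preoperatively and postoperatively at six weeks, 12 weeks and 12 months". The abstract agrees: "Clinical outcome measures will be administered preoperatively and at 6, 12 and 52 weeks postoperatively".

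Two other sections bring participants into contact with the study more often:

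- Functional evaluations are "performed by a blinded physiotherapist preoperatively and at 2, 4, 6, 12, 26 and 52 weeks after TKA".
- Under Economic evaluation, patient-specific resource use after discharge is collected "using a resource use questionnaire that will be administered at 2, 4, 6, 12, 26 and 52 weeks".

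The same section names, after incremental cost per unit of knee ROM as its primary outcome, a secondary one: the "incremental cost per quality-adjusted life year (QALY) gained over the period of the primary study". Its utilities come from the EQ-5D-5L: a UK value set "will be used to convert the individual responses to the EQ-5D-5 L at each time point". Study duration sets the horizon: "Each individual will be followed for 12 months". The article gives no rule for turning the utilities into QALYs.

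**The concern.** Cost per QALY divides a cost difference by a QALY difference. Here the costs are collected at 26 weeks and the utilities are not. Whatever happens to quality of life between weeks 12 and 52 has to be inferred from the two ends.

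The article gives some reason to think this interval is not quiet:

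- The ROM section says that recovery of knee motion plateaus at 12 months, so change is still under way after week 12.
- The Background says that poor ROM found at three months may prompt rehabilitation before manipulation under anaesthesia or revision is needed. Any such care would fall largely in the gap.
- Skate participants may receive additional physiotherapy, and standard care offers four individual options after discharge, so the two arms need not follow the same path.

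The costs of such events would reach the questionnaires at 26 and 52 weeks. A loss or gain in utility that arose after week 12 and had gone by week 52 would not be recorded. At stake are the incremental QALY and the acceptability curves built on it.

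**Working it through.** The article states no figure for this point, so there is none to reproduce.

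**Inputs from the article.** EQ-5D-5L at weeks 0, 6, 12 and 52; resource use at weeks 2, 4, 6, 12, 26 and 52; horizon 52 weeks.

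**Assumptions.** Linear interpolation between measured utilities (area under the curve), and a true path that is piecewise linear with a bend at week 26. The article gives no utility values, so d = 0.02 to 0.08 is an assumed range.

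**1. Unobserved share.** (52 − 12)/52 = 40/52 = 0.769, or 77%. This needs no interpolation rule.

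**2. Weight of each measurement in the QALY.** Each value carries half of the interval on either side, divided by 52.

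| Week | Current schedule | With week 26 added |
|---|---|---|
| 0 | 3/52 = 0.058 | 0.058 |
| 6 | 6/52 = 0.115 | 0.115 |
| 12 | 23/52 = 0.442 | 10/52 = 0.192 |
| 26 | not measured | 20/52 = 0.385 |
| 52 | 20/52 = 0.385 | 13/52 = 0.250 |

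On the current schedule the week-12 and week-52 values together carry 43/52 = 0.827 of the weight.

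**3. Effect of a departure at week 26.** If the true utility at week 26 lies d away from the 12-to-52-week line, the missed area is a triangle with a 40-week base: 0.5 × (40/52) × d = 0.385 × d.

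- d = 0.02: 0.008 QALY
- d = 0.05: 0.019 QALY
- d = 0.08: 0.031 QALY

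Illustration with assumed values: utility is 0.70 at week 12 and reaches a plateau of 0.80 by week 26. The line at week 26 is 0.70 + 0.10 × 14/40 = 0.735, so d = 0.065 and the participant's QALY is understated by 0.385 × 0.065 = 0.025.

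**4. Between-arm effect.** The size of the bias in the incremental QALY is 0.385 × (difference in mean d between the arms). With equal departures it is zero.

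**5. First six weeks.** If utility departs from the 0-to-6-week line by d at both week 2 and week 4, the missed area is (1 + 2 + 1) × d weeks, or 4/52 × d = 0.077 × d. At d = 0.05 that is 0.004 QALY.

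**6. After adding week 26.** The intervals become 14 weeks (27%) and 26 weeks (50%). The longest unobserved stretch falls from 40 to 26 weeks.

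**The case against.** The case against is substantial.

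- **Nothing is contradicted.** Resource use accumulates and has to be asked about in successive periods, while utility is a state sampled at chosen times. The two schedules need not match. This stands: a reader might infer an inconsistency between the sections, and there is none.
- **The interpolation rule is not in the article.** A reader might infer that 77% of each QALY is a straight line. The article says only that responses are valued at each time point, and the rule may sit in an analysis plan that is not shown. This stands. The 77% describes missing observation; 0.385 × d is conditional on linear interpolation.
- **A six-month difference is not simply invisible.** A difference still present at week 12 or week 52 carries into the interpolated period. Only a departure from the line that differs between arms biases the comparison. This stands.
- **A large arm-specific departure is not foreseen.** The Background cites a trial in which one-to-one treatment was not superior to group or monitored home programmes on self-reported outcomes up to 12 months. That tempers the expected size, but it concerns other programmes and does not establish that the arms here follow the same path.
- **Sampling error may be larger.** With 55 per arm and an assumed one-year QALY SD of 0.10 to 0.20, the 95% half-width is 1.96 × SD × √(2/55), about 0.037 to 0.075, above the range of 0.008 to 0.031. This is fair on scale. But the interval does not allow for a systematic shift.
- **The early weeks.** It is tempting to say that the programmes differ most in early recovery, so that weeks 2 and 4 matter most. No part of the article says when the contrast is largest, and the effect computed above is small.

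**Conclusion.** The schedule facts are firm, since the abstract and the outcome section agree. The assessment schedule figure is not available, and the point does not depend on it. No utility is observed for 40 of the 52 weeks behind the cost-per-QALY outcome, although a visit and a cost questionnaire already fall inside the gap.

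The size is modest and conditional. It rests on linear interpolation and an assumed d, and the incremental QALY is biased only by the part of d that differs between arms. The documents do not show that it will differ.

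A reader might conclude that the whole economic evaluation is compromised. It is not: cost per QALY is its secondary outcome, and neither the primary economic outcome nor the trial's primary endpoint uses the EQ-5D-5L. The point is still worth acting on, because cost-effectiveness is a stated aim of the trial. The planned multiple imputation also has no observed week-26 utilities to draw on if that time point is collected in nobody.

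**What to change.** Add the EQ-5D-5L to the existing 26-week visit, alongside the resource use questionnaire, and include that value in the QALY calculation. State the calculation rule, for example area under the curve over weeks 0, 6, 12, 26 and 52. The OKS, KOOS and PASS can keep their present schedule.

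Adding the EQ-5D-5L at weeks 2 and 4 is optional, with a gain of at most about 0.077 × d if both weeks depart by d.

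The cost is a five-item form at a visit already attended: a few minutes of participant time and an amendment to the schedule of events, with no extra visit, staff or procedure. The change narrows the gap but does not close it, since weeks 26 to 52 would still rest on two values.
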